**8 Safety evaluation:**

8.1 Nature and frequency of adverse reactions and events.

Adverse reaction assessment: The investigator assesses and records the severity of discomfort according to with following criteria, and the subjects should visit the doctor’s office regularly or at any time:

0= no discomfort;

1= slight discomfort, not affecting daily life and work;

2= moderate discomfort, affecting daily life and work;

3= severe discomfort, significantly affecting life and fitness status (requiring bed rest);

4= Life-threatening.

8.2 Tolerability assessment:

After the end of treatment, the physician in charge will conduct comprehensive evaluation on the tolerability of each subject according to the following criteria;

0= well tolerated, with no adverse reaction;

1= good tolerance, with slight adverse reaction which does not need treatment;

2= moderate tolerance, with adverse reaction needing to be treated;

3= poor tolerance, with adverse reaction which results in drug discontinuation.

8.3 Unexpected events:

The unexpected events occurring to the subjects during the course of treatment, such as cerebrovascular accident, automobile accident and death should be recorded.

8.4 Adverse event relevance:

The investigator should evaluate the relationships between adverse events (AEs) and the investigational drug / concomitant medication by reference to the 5-grade classification criteria below:

1) Definitely related: the reaction occurs following a reasonable temporal sequence from administration of the drug and falls into the known reaction types of the suspected drug; the reaction improves after drug withdrawal but occurred again after resumption of drug administration.

2) Possibly related: the reaction occurs following a reasonable temporal sequence from administration of the drug and falls into the known reaction types of the suspected drug; the reaction could also be caused by the subject’s clinical state or other therapeutic methods.

3) Possibly unrelated: the reaction occurs not quite following a reasonable temporal sequence from administration of the drug and does not fall into the known reaction types of the suspected drug completely; the reaction could also be caused by the subject’s clinical state or other therapeutic methods.

4) Definitely unrelated: the reaction occurs not following a reasonable temporal sequence from administration of the drug and falls into the known reaction types of other drugs than the investigational drug; the reaction could also be caused by the subject’s clinical state or other therapeutic methods, and the disease condition improves or symptoms of the reaction disappears after withdrawal of other therapeutic methods but appears again after resumption of other therapeutic methods.

5) Not evaluable: the reaction occurs not following a definite temporal sequence from administration of the drug and resembles the known reaction types of the drug, but it could also be caused by other drugs used at the same time.

The 1), 2) and 5) of the above 5 items are recorded as adverse reactions (ARs) of the drug.

Incidence of ARs: Number of patients experiencing ARs / Total number of patients × 100%.

8.5 Assessment of infection and other serious adverse events (SAEs):

Close attention should be paid to the occurrence of infection during observation and make statistics accordingly; in case of any serious adverse reaction (SAR) (e.g., serious infection and serious local reaction), the drug should be withdrawn immediately, the sponsor contacted as soon as possible and symptomatic treatment given promptly. If it is a mild or moderate AR, symptomatic treatment may be given first for observation; if the symptom is still not alleviated, the drug should be withdrawn and the changes in the disease condition should continue to be observed.

Re-examination should be performed immediately if the laboratory findings are slightly abnormal, e.g., elevated transaminase level; if the abnormalities persist, symptomatic treatment should be given for observation, and observation of changes in the disease conditions continued. The drug should be withdrawn immediately if the abnormalities continue to worsen or serious abnormalities occur.

8.6 Assessment of SAEs:

SAE is defined as any AE that occurs at any dose of the investigational drug or at any time during observation, including those that are immediately life-threatening, necessitate hospitalization or prolonged hospitalization, lead to disability, or cause congenital malformation or permanent loss of function.

In case of serious adverse events (related or unrelated to drugs), they should be reported to the Medical department of Shanghai CP Guojian Pharmaceutical Co., Ltd. and to the China Food and Drug Administration within 24 hours, and a written report should be made within 7 days.

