**5. Test method and course of treatment**

5.1 Test method:

The trial is a randomized, controlled, open-label, multicenter clinical study. Qualified subjects after screening will be randomly divided into 3 groups (Groups A, B and C) using centre-stratified block-permuted randomization, with 30 patients in each group and 90 patients in total:

5.2 Drug usage:

1. In MTX therapy, the initial dose is 10mg/ week, which will gradually be increased to 15 mg/ week (in Week 4);
2. At the same time, 25mg of RhTNFR:Fc (trade name: Yisaipu) will be injected subcutaneously each time, twice a week for treatment.
3. The subjects will be treated with the combined use of MTX according to the above regimen until Week 52, and endpoint evaluation will be conducted. The dose of MTX could be reduced for safety reasons. If the subjects could not tolerate the dose reduction, the event could be recorded as an adverse event. After reduction, the dose could be restored to the prescribed dosage when the investigator thinks it is appropriate.
4. Diagram of drug usage:

Group A:

(RhTNFR:Fc + MTX group), 52 weeks; n=30

Group B:

"MTX monotherapy"; n=30

(RhTNFR:Fc + MTX group)

Group C:

"MTX monotherapy"; n=30

Baseline

52 weeks

24 weeks

4 weeks

12 weeks

36 weeks

MTX dose increase stage: MTX will be increased from 10 mg/ week to 15 mg/ week

Note: Folic acid at 5 mg/ week will be given on the Day 2 of MTX administration in the trial.

5.3 Criteria for drug withdrawal:

If one of the following conditions occurs, the investigator may consider drug discontinuation for observation:

1. A serious adverse event occurs, and it has certain relationship with the investigational drug;
2. An adverse drug reaction occurs, and effective remission cannot be achieved after symptomatic treatment;
3. Laboratory tests: transaminase > 3 times the normal value or WBC < 3×109 /L, or PLT < 100×109 /L;
4. The subject has other diseases, and the investigational drug may aggravate the condition.

5.4 Withdrawal from the trial:

For the patients who withdraw during the trial, the investigator must record the reason and date of withdrawal in detail. Patients who may withdraw during the trial can be divided into the following categories:

- 1. Patients found to fail to meet the inclusion/exclusion criteria during the trial;

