**9. Statistical methods:**

9.1 Selection of statistical analysis data:

Intent-to-treat (ITT): all subjects eligible and enrolled after screening and having taken at least one dose of the drug and received at least one post-treatment effectiveness evaluation; LOCF (last observation carry-forward) will be adopted for those subject’s data not observed during the whole treatment course, that is, estimating the missing values of important indicators using the closest observed data. The ITT analysis will be used in this trial.

Safety population: it includes all subjects having taken at least one dose of the drug and received at least one post-treatment safety evaluation.

9.2 Statistics Analysis Plan:

Statistical analysis will be carried out using the SAS statistical analysis software. A sample size of 90 patients was estimated for the open label period with the assumption that mean mTSS CRF was -0.5±1.0 in the MTX plus rhTNFR:Fc group, and 2.5±5.0 in the MTX group at week 52. A sample size of 25 patients per treatment group was calculated to be necessary for more than 80% power to reject the null hypothesis of no difference among the treatment groups with an α of 0•05. Assuming loss of patients, the study required a minimum of 30 patients in each group. Two-sided test will be used for all statistical tests, and the difference tested will be considered as statistically significant if the P value is equal to or less than 0.05. Measurement data will be statistically described using mean±SD (standard deviation). Paired t-test will be used for intra-group differences before and after the treatment. Enumeration data will be statistically described using frequency (constituent ratio).

Dropout analysis: Calculate the dropout rates and the rates of dropout due to AE.

Efficacy analysis: The paired t test or nonparametric test or chi-square test will be used to evaluate the efficacy indexes.

Safety analysis: Calculate the incidence rate of adverse events and tabulate the AEs occurring during the trial, normal/abnormal changes in laboratory findings before and after the trial, as well as relationships of abnormal changes with the investigational drug

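### The 8.1 severity scale has no laboratory criterion, so a symptom-free laboratory reaction short of life-threatening is graded 0 and its degree appears in no stated safety summary

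*Protocol*

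**What the plan says.** All references are to the protocol.

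- **Section 8.1** sets the scale: "The investigator assesses and records the severity of discomfort according to with following criteria". It runs from "0= no discomfort" through "1= slight discomfort, not affecting daily life and work", then moderate and severe discomfort, to "4= Life-threatening". No grade mentions a laboratory value, and no other severity scale for adverse events is given.
- **Section 5.3** lists laboratory conditions under which the investigator may consider stopping the drug. The list opens with "Laboratory tests: transaminase > 3 times the normal value" and adds WBC below 3×10^9/L and platelets below 100×10^9/L.
- **Section 8.2** gives one tolerability score per patient after treatment ends, according to whether a reaction needed no treatment, needed treatment, or led to stopping.
- **Section 8.5** has a separate paragraph on laboratory findings. It distinguishes slight from serious abnormalities in words, without figures, and says: "The drug should be withdrawn immediately if the abnormalities continue to worsen or serious abnormalities occur".
- **Section 8.4** defines adverse reaction incidence as a count of patients over the total, without reference to grade.
- **Section 9.2** plans the incidence of adverse events, a tabulation of them, "normal/abnormal changes in laboratory findings before and after the trial", and the relationship of abnormal changes to the drug. It names no analysis by 8.1 grade.

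**The concern.** Raised transaminases and low blood counts can occur without the patient feeling anything. The protocol itself treats them as important enough to be grounds for considering discontinuation. Yet the instrument that investigators must use to record severity cannot register them between nothing and a threat to life. Read literally, it ranks a symptom-free transaminase at 4 times normal below slight soreness at an injection site.

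Evaluating safety is part of the trial's title, and laboratory change is one of the two safety evaluation items in the Summary. What is at stake is whether a reader of the results could tell a marginal laboratory abnormality from one beyond the protocol's own limits.

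**Working it through.** This is a check of wording. The protocol states no figure to reproduce.

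**Step 1. Apply 8.1 literally to three invented records.**

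| Record | Beyond a 5.3 limit? | 8.1 grade |
| --- | --- | --- |
| ALT 4 times normal, feels well, not life-threatening | Yes (limit: 3 times) | 0 |
| WBC 2.5×10^9/L, feels well, not life-threatening | Yes (limit: 3×10^9/L) | 0 |
| Slight injection-site discomfort, daily life unaffected | No | 1 |

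Grades 1 to 3 all require discomfort, so a silent laboratory reaction can take only the values 0 and 4.

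**Step 2. Look for the degree elsewhere.**

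- *Adverse reaction incidence (8.4):* shows that a reaction occurred, not how large it was.
- *Tolerability (8.2):* scores 2 or 3 if the reaction was treated or the drug was stopped. This reflects the action taken, not the size of the abnormality. Because 5.3 is discretionary, a patient beyond a limit who continues untreated need not reach either score.
- *Laboratory findings (8.5):* uses words without cut-points and does not say whether a value beyond a 5.3 limit counts as serious.
- *Laboratory table (9.2):* normal or abnormal only.

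**Step 3. Test the 9.2 table against the entry criteria.** Section 4.2 excludes ALT or AST only above 2 × ULN, so entry with values between 1 and 2 × ULN is allowed. The 5.3 limit is 3 times the normal value, taken here as 3 × ULN.

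| Entry (× ULN) | On treatment (× ULN) | Beyond 5.3 limit? | 9.2 category |
| --- | --- | --- | --- |
| 1.5 | 1.6 | No | abnormal → abnormal |
| 1.5 | 4 | Yes | abnormal → abnormal |
| 0.8 | 1.2 | No | normal → abnormal |
| 0.8 | 4 | Yes | normal → abnormal |

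Within each pair the table cannot separate the value inside the limit from the one beyond it. In the first pair it shows no change at all.

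For WBC and platelets, the entry limits in 4.2 equal the 5.3 limits, so no eligible patient starts beyond them. The two-category table still does not say whether an abnormal on-treatment count crossed them.

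**Step 4. Illustrate the size.** If k of the 30 patients in a group had a silent value beyond a 5.3 limit, short of life-threatening, the share graded 0 despite being beyond the limit is k/30:

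- k = 1: 1/30 = 3.3%
- k = 3: 3/30 = 10%
- k = 6: 6/30 = 20%

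The counts are assumed. The protocol gives no expected rate, so this is not a prediction.

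**The case against.** The strongest reply is that laboratory toxicity has its own route. The Summary lists laboratory changes of clinical significance beside adverse reactions, 8.5 treats them in their own paragraph, and 9.2 tabulates them with their relationship to the drug. A discomfort scale for symptoms next to a laboratory evaluation is a coherent, if coarse, design. This stands as far as occurrence goes. It does not supply the degree, because that route has two categories.

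Four stronger readings are tempting, and the documents do not support them:

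- *Reported severity results understate liver and blood toxicity.* Section 9.2 names no table by 8.1 grade, so no planned result is shown to be understated. Only a summary that used those grades would be affected.
- *Silent toxicity vanishes from the safety results.* Incidence does not depend on grade, the laboratory table includes such findings, and 8.2 registers those treated or stopped.
- *A rise that resolves by Week 52 reads as normal to normal.* This takes the 9.2 comparison to mean baseline against Week 52 only. Section 6.2 speaks of Weeks 12, 24, 36 and 52 alike as after treatment, so the phrase need not exclude the earlier visits.
- *8.1 and 8.2 contradict each other when one event scores 0 and 3.* They measure different things, discomfort and action taken, so the scores may differ.

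It can also be said that worst-value tables are commonly left to a SAP, which is not at hand. That is fair for the layout of a table. The scale in 8.1 is different: it is a stated rule applied by investigators during the trial. A later analysis could reclassify the laboratory values, but the investigator's recorded severity would remain 0.

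**Conclusion.** The point holds in a limited form. Section 8.1 assigns 0 to any symptom-free laboratory reaction short of life-threatening, even one beyond the limits in 5.3, and no stated summary shows how large the abnormality was. What is lost is the degree of silent laboratory toxicity, not its occurrence.

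The conclusion rests on a literal reading of the scale and on taking the normal value in 5.3 as the upper limit of normal. The 3 to 20 percentage points above depend on assumed counts of 1 to 6 patients per group and show scale only.

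Severity is minor. The primary endpoint, the sample size and the analyses that 9.2 names are not affected.

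**What to change.** - **Section 8.1:** keep the discomfort scale for symptomatic reactions. State that laboratory reactions are graded by the size of the abnormality whether or not there are symptoms, and that no recorded reaction is graded 0.
- **Sections 5.3, 8.2 and 8.5:** reconcile them with the revised 8.1, so that it is clear how a value beyond a 5.3 limit relates to the severity grade, the tolerability score and the words slight and serious in 8.5. How they are aligned is a clinical decision for the sponsor. No new threshold is proposed here.
- **Section 9.2:** tabulate each patient's worst on-treatment value across Weeks 12, 24, 36 and 52 against baseline (highest transaminase as a multiple of the normal limit, lowest WBC, lowest platelets). Include the number per group beyond the limits already written in 5.3.

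The cost is protocol and case report form wording and one more table. Blood count and biochemistry are already scheduled at all four visits, so no extra sampling is needed. The small downside is that the reported safety profile may look less favourable.

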**9. Statistical methods:**

9.1 Selection of statistical analysis data:

Intent-to-treat (ITT): all subjects eligible and enrolled after screening and having taken at least one dose of the drug and received at least one post-treatment effectiveness evaluation; LOCF (last observation carry-forward) will be adopted for those subject’s data not observed during the whole treatment course, that is, estimating the missing values of important indicators using the closest observed data. The ITT analysis will be used in this trial.

Safety population: it includes all subjects having taken at least one dose of the drug and received at least one post-treatment safety evaluation.

9.2 Statistics Analysis Plan:

Statistical analysis will be carried out using the SAS statistical analysis software. A sample size of 90 patients was estimated for the open label period with the assumption that mean mTSS CRF was -0.5±1.0 in the MTX plus rhTNFR:Fc group, and 2.5±5.0 in the MTX group at week 52. A sample size of 25 patients per treatment group was calculated to be necessary for more than 80% power to reject the null hypothesis of no difference among the treatment groups with an α of 0•05. Assuming loss of patients, the study required a minimum of 30 patients in each group. Two-sided test will be used for all statistical tests, and the difference tested will be considered as statistically significant if the P value is equal to or less than 0.05. Measurement data will be statistically described using mean±SD (standard deviation). Paired t-test will be used for intra-group differences before and after the treatment. Enumeration data will be statistically described using frequency (constituent ratio).

Dropout analysis: Calculate the dropout rates and the rates of dropout due to AE.

Efficacy analysis: The paired t test or nonparametric test or chi-square test will be used to evaluate the efficacy indexes.

Safety analysis: Calculate the incidence rate of adverse events and tabulate the AEs occurring during the trial, normal/abnormal changes in laboratory findings before and after the trial, as well as relationships of abnormal changes with the investigational drug

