  2. Treatment discontinuation > 4 weeks during the medication due to adverse drug reaction or other reasons (e.g. the treatment has to be discontinued due to occurrence of other disease, migration to other places and loss to follow-up); or within 24 weeks, the accumulated duration of drug discontinuation has exceeded 8 weeks;
  3. Subjects who withdraw the drug by themselves and give up continuing the trial;
  4. Due to serious adverse drug reaction, the drug must be withdrawn in advance.
  5. Those with poor compliance and failing to take the drug according to the schedule or design;
  6. Those with concurrent occurrence of other serious diseases and the investigator considers inappropriate to continue the medication;
  7. Those failing to complete all the examination items as required and thus not evaluable.

5.5 Trial assessments:

The screening visit will be completed within 3 weeks (21 days) before the first administration of the investigational drug. The baseline visit and randomization will be conducted on the day of the first administration, and informal visits will be conducted every 4 weeks to understand the medication and adverse events of the subjects. Formal visits will be conducted every 12 weeks, and the visit results will be recorded. The endpoint visits will be conducted at week 52. In addition to the baseline, the time window for each visit is ±7 days (based on the baseline).

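### The set that section 9.1 labels ITT is a modified set, and section 5.4 provides for no films after withdrawal, so the randomised comparison is compromised, though not lost

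*Protocol*

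**What the plan says.** **Analysis set.** Protocol section 9.1 defines its intent-to-treat population as "all subjects eligible and enrolled after screening and having taken at least one dose of the drug" who have also "received at least one post-treatment effectiveness evaluation". For values not observed, "LOCF (last observation carry-forward) will be adopted". The section closes with "The ITT analysis will be used in this trial", and no other efficacy set is named.

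**Withdrawal.** Section 5.4, on withdrawal from the trial, opens its list with "Patients who may withdraw during the trial can be divided into the following categories". The categories include:
- "Patients found to fail to meet the inclusion/exclusion criteria during the trial";
- treatment stopped for more than 4 weeks, or for more than 8 weeks in total within 24 weeks;
- early stopping because of a serious adverse drug reaction;
- "Those with poor compliance and failing to take the drug according to the schedule or design";
- "Those failing to complete all the examination items as required and thus not evaluable".

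The only duty that section 5.4 places on the investigator is to record why and when the patient left.

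**Schedule.** Section 5.5 and the flow chart in Attachment I put the first formal visit with an efficacy evaluation at Week 12. The four-weekly informal visits cover medication and adverse events only. Hand and wrist films are taken at baseline, Week 24 and Week 52. The primary endpoint in section 7.1 is the Sharp score. Treatment is open label.

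**The concern.** An intent-to-treat set keeps every randomised patient in the assigned group, so that nothing after randomisation decides who is compared. The set in section 9.1 applies two conditions that are met or failed after randomisation: taking a dose and reaching an efficacy evaluation. It also carries an eligibility condition whose timing is unclear. In an open-label trial, staying to Week 12, compliance and a late judgement of ineligibility can all depend on the known arm.

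Section 5.4 adds to this. It treats events linked to tolerance and response as the end of participation and provides for no later films. The two rules meet on the primary endpoint: early leavers are omitted, and those who leave somewhat later are filled in from a baseline film. With 30 patients per arm, a few such cases move the contrast, and the result would still be reported as intent-to-treat.

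**Working it through.** **Inputs.** From section 9.2: mean change in the Sharp-type score at Week 52 of -0.5 (SD 1.0) on the combination and 2.5 (SD 5.0) on MTX; 25 per group for more than 80% power, two-sided α 0.05; a minimum of 30 per group to allow for loss. The planned difference is 2.5 - (-0.5) = 3.0.

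**1. The plan's own figures.** The standard error of the difference with 25 per group is √((1.0² + 5.0²)/25) = √(26/25) = 1.02, and 3.0/1.02 = 2.94. An unequal-variance t-test (about 25.9 degrees of freedom) has 80.8% power with 25 per group and 79.1% with 24. The stated 25 is reproduced. Going from 25 to 30 leaves room for 5/30 = 16.7% per group. That rate is inferred; the protocol gives none.

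**2. What the rules do, by time of leaving.**

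| Time of leaving | In the section 9.1 set? | Film available to carry forward |
|---|---|---|
| Before the Week 12 evaluation | No | – |
| Weeks 12 to 24 | Yes, on the clinical evaluation | Baseline only, so change = 0 |
| Weeks 24 to 52 | Yes | Week 24 film |

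Patients later found ineligible are out if the eligibility condition means confirmed eligible, and in if it means judged eligible at screening. The text allows both. Randomisation takes place on the day of first dosing (section 5.5), so undosed patients should be few.

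**3. Change set to 0.** Assume that m of 30 MTX patients leave between Weeks 12 and 24 and that the others average 2.5. The MTX mean is (30 - m) × 2.5/30.
- m = 1: mean 2.42, difference 2.92
- m = 3: mean 2.25, difference 2.75
- m = 5: mean 2.08, difference 2.58

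If the combination arm has the same number set to 0, its mean is (30 - m) × (-0.5)/30, and the differences are 2.90, 2.70 and 2.50.

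**4. Omission.** Assume that the full MTX arm averages 2.5 and that one patient who leaves before Week 12 is omitted.
- The omitted patient would have scored 5.0: (75 - 5.0)/29 = 2.41, difference 2.91.
- 7.5: (75 - 7.5)/29 = 2.33, difference 2.83.
- 2.5: the mean stays 2.5, the difference stays 3.0, and there is no bias.

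Omission from the other arm works the opposite way. If one combination patient who would have scored 2.5 is omitted, the rest average (30 × (-0.5) - 2.5)/29 = -0.60, and the difference rises to 3.10.

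**5. How many patients could be affected.** If 5 losses per arm fell evenly over 52 weeks (an assumption), 5 × 12/52 = 1.2 would leave before Week 12, another 1.2 between Weeks 12 and 24, and 5 × 28/52 = 2.7 later. On that assumption the one-patient cases in steps 3 and 4 are the central ones. Five patients is the upper end.

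**The case against.** **Section 5.4 may only classify reasons.** It speaks of patients who may withdraw, its treatment-stopping category has thresholds, and missed examinations count only when the patient is thereby not evaluable. Section 5.3 treats stopping drug for observation separately, and section 8.5 continues observation of the disease condition after some drug withdrawals. This stands in part. A reader might infer that any missed examination or any interruption ends participation, and the text does not say so. A reader might also infer that films are forbidden after withdrawal; the protocol is only silent. But these categories stand under the heading of leaving the trial, and neither section 5.3 nor section 8.5 mentions films or efficacy visits.

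**Last observation carried forward keeps most leavers in.** This also stands. It is tempting to delete all 5 of 30 MTX losses. If they progressed twice as fast as those kept, the kept mean would be 2.5/(1 + 1/6) = 2.14, which is 14% below 2.5. That is not the rule in section 9.1, which keeps anyone with one post-treatment evaluation. Nor does the plan state a 17% loss; that figure is only the gap between 25 and 30.

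**No bias towards the drug is shown.** Correct. Most of the illustrations shrink the difference, and one enlarges it.

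**A statistical analysis plan could redefine the set.** It could correct the label. It could not recover films that were never taken, and it is the protocol that fixes the set and names it ITT.

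**Conclusion.** The point holds in a limited form. The only efficacy set is a modified one under an intent-to-treat label, and the protocol provides for no films after withdrawal for reasons that may be related to treatment. A reader might conclude that the randomised comparison is lost. The documents do not support that: undosed patients should be few, most leavers stay in through the carried-forward value, and if those omitted resemble those kept, omission causes no bias. Compromised is the right word.

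The size cannot be computed, because the protocol gives no dropout rate and no information on how leavers progress. Under the assumptions shown, one affected MTX patient moves the planned difference of 3.0 by about 0.1, and five set to 0 in that arm move it to 2.58. The direction depends on which arm loses patients and why.

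**What to change.** - **Section 9.1:** define ITT as all randomised patients, analysed in the assigned group. Rename the present set modified ITT and keep it for a sensitivity analysis.
- **Section 5.4:** state that stopping drug, poor compliance, later-found ineligibility or a missed examination does not end scheduled follow-up. The Week 24 and Week 52 films and the clinical visits continue unless the patient withdraws consent.
- **Unchanged:** all drug-stopping rules, including how treatment is handled in patients found ineligible; the sample size; and the visit schedule.

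The cost is protocol wording and some follow-up effort for a few patients. The films and visits are already on the schedule in Attachment I. The section 5.4 change must be in place before patients leave, because missed films cannot be taken later.
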